### Exacerbations of COPD

Patients have been requested to record their exacerbation information in the patient diary and collected at every follow-up. Acute exacerbation of COPD is considered to be due to exacerbation of respiratory symptoms (cough, expectoration, expectoration, wheezing, dyspnea, at least two new symptoms or aggravation of the original symptoms, and lasting for at least 48 h). Meanwhile, the following diseases should be ruled out: left or right ventricular dysfunction, pulmonary embolism, pneumothorax, pleural effusion, and arrhythmia [1, 24]. The duration of COPD exacerbation was defined as the date from the onset of acute exacerbation to the end of the event. The duration of hospitalization was defined as the time from admission to that of discharge from the hospital. The interval between the two times of COPD exacerbation was defined as the duration between the previous exacerbation event and the next event, and it should be noted that if the interval between two events was less than 7 days, they were regarded as the same event [1].

The severity of COPD exacerbation was categorized as mild, moderate, and severe as follows: mild, adding other common medications for COPD without outpatient hospital visit or hospitalization; moderate, exacerbation requiring outpatient or emergency room visit and the use of antibiotics and/or systemic glucocorticoids; or severe acute exacerbation requiring hospitalization [25]. Specifically, the date of each exacerbation and admission are being obtained, and the times to first exacerbation and admission will be calculated.

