### Sample size and statistical methods

We determined the sample size with regard to the primary endpoint according to the PANTHEON study [9]. The sample size was calculated based on the difference between the peak and trough values of FEV_1_ in two groups: patients with mild-to-moderate COPD were included in this study. According to the early clinical trials, FEV_1_ of GOLD II COPD patients in the experimental group and the control group after 2 years were compared. The difference in valley value was 100 ml (standard deviation was 450 ml). Assuming that the test water is 5% and the test efficiency is 80%, each treatment group needs 318 patients to detect the difference in FEV_1_ trough between the two groups. Assuming a 35% drop-off rate, each group needs to be randomized at least 489 patients. Therefore, the overall sample size of this study needs 1000 patients.

Repeated measurement analysis of variance will be used to analyze the valley and peak value of FEV_1_, CCQ, and CAT data assessments. The annual decline rate of FEV_1_, FVC, and FEV_1_/FVC was analyzed by the random coefficient regression model. Assuming that the treatment effect changes linearly with the treatment time, the annual decline rate is represented by the regression coefficient of the model. The number and degree of acute exacerbation were compared by adjusted treatment exposure dose and over discrete Poisson regression. A log-rank test was used to compare the interval time of the first exacerbation of COPD. Fisher’s exact probability method was used to analyze the interval and duration of acute exacerbation of COPD, severity, and the use of rescue drugs. The frequency of rescue drugs will be further described. Before locking the database, the analysis plan will be explained in detail in a separately prepared statistical analysis plan (SAP).

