Target sample size	1000
Recruitment status	Recruiting
Primary outcome(s)	The difference of FEV_1_ (including trough and peak) at 24 months from baseline and the number of acute exacerbations COPD within 24 months between two groups
Key secondary outcomes	Annual decline of FEV_1_, forced vital capacity (FVC) and FEV_1_/FVC (including trough and peak); duration, interval, and severity of COPD exacerbations

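### Fisher's exact test is named for exacerbation duration and interval, which are elapsed times, and for event-graded severity with no stated unit of analysis

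*Protocol article*

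**What the plan says.** Three parts of the protocol article bear on this point.

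- **Method.** Under Sample size and statistical methods, Fisher's "exact probability method was used to analyze the interval and duration of acute exacerbation of COPD, severity, and the use of rescue drugs". Two sentences earlier, the same paragraph says: "The number and degree of acute exacerbation were compared by adjusted treatment exposure dose and over discrete Poisson regression". Time to the first exacerbation has its own log-rank test.
- **Definitions.** Under Exacerbations of COPD: "The duration of COPD exacerbation was defined as the date from the onset of acute exacerbation to the end of the event". Next: "The interval between the two times of COPD exacerbation was defined as the duration between the previous exacerbation event and the next event". A patient can have several events, because only close ones are merged: "if the interval between two events was less than 7 days, they were regarded as the same event". Grading is in three ordered classes attached to each event: "The severity of COPD exacerbation was categorized as mild, moderate, and severe as follows".
- **Status.** Table 1 (Ethics and dissemination) lists "duration, interval, and severity of COPD exacerbations" among the key secondary outcomes.

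The article gives no cut-points for the times and does not say whether the unit of analysis is the patient or the event. It leaves detail to a separate SAP, which is not shown.

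**The concern.** Fisher's test works on a contingency table. A number of days is not a category, so the test can be applied to duration or interval only after the times are cut into classes. That discards information, and the test itself yields no effect in days. Interval has a further difficulty. The gap after a patient's last event is still open when follow-up ends, and a table of cut gaps has no proper place for it. The plan already uses a censored-data method for time to first exacerbation, so this treatment of the later gaps is inconsistent.

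Severity is different, because it is categorical by definition. The question there is the unit. A table of events treats several events from one patient as independent, and that would make the p-value too small when severity is correlated within a patient. Finally, *degree* goes to Poisson regression and *severity* to Fisher's test, so a reader cannot tell which analysis answers the severity question.

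**Working it through.** **The plan's own figure.** The document states no error rate or power for these outcomes. The only figure that can be recomputed is the FEV1 sample size, based on "Assuming that the test water is 5% and the test efficiency is 80" per cent, a difference of 100 ml and an SD of 450 ml. With a two-sided test, n = 2 × (1.96 + 0.84)² × 450² / 100² ≈ 318 per group, as stated. Then 318 / 0.65 = 489.2, stated as 489. It reproduces and has no bearing on this point.

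**Step 1: scale against test.**

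| Outcome | Scale as defined | Exists for | Fisher's test |
|---|---|---|---|
| Duration | elapsed time per event | patients with at least 1 event | does not fit without cut-points |
| Interval | gap between events, censored at end of follow-up | complete only with at least 2 events | does not fit without cut-points |
| Severity | 3 ordered grades per event | patients with at least 1 event | valid once per patient (ignores order); not valid on pooled events |
| Rescue drug use | yes/no per patient is possible | all patients | valid |

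**Step 2: cost of cutting a time, one value per patient.** All inputs are assumed: normal values, split at the pooled median, 4,000 simulated trials per setting.

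| Patients per arm with a value | Shift (SD) | Median split + Fisher | Wilcoxon |
|---|---|---|---|
| 100 | 0 | 3.6% | 4.8% |
| 200 | 0 | 3.3% | 4.8% |
| 100 | 0.40 | 56.2% | 80.0% |
| 200 | 0.28 | 55.5% | 77.3% |

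False positives do not rise; Fisher's test is slightly conservative. The loss is 80.0 − 56.2 = 23.8 points of power in one setting and 77.3 − 55.5 = 21.8 in the other.

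**Step 3: severity on pooled events.** Assumed inputs: no treatment effect, 500 per arm, mean m = 0.6, 1.0 or 2.0 events per patient over 2 years, negative binomial dispersion d = 0.5, 1 or 2, a binary severity split with probability 0.4, and a within-patient correlation (ICC) of severity. The documents give none of m, d or ICC. There were 36 scenarios with 700 simulated trials each. The simulation standard error near 5% is √(0.05 × 0.95 / 700) ≈ 0.8 points.

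| ICC | Fisher on pooled events, type I error |
|---|---|
| 0 | 2.7–6.1% |
| 0.1 | 5.4–11.0% |
| 0.3 | 7.1–21.1% |
| 0.5 | 8.3–31.6% |

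With one yes/no value per patient (any event of the higher severity class, all 500 per arm), the range over the same scenarios is 2.7–5.6%, so there is no inflation beyond simulation error.

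**Step 4: analytic check.** Design effect: DEFF = 1 + ICC × m × (1 + d). For example, m = 1.0, d = 1, ICC = 0.1 gives 1 + 0.1 × 1.0 × 2 = 1.2. With m = 1.0, d = 2, ICC = 0.5 it is 1 + 0.5 × 1.0 × 3 = 2.5. The type I error is approximately 2 × [1 − Φ(1.96 / √DEFF)]:

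- DEFF 1.2: 7.4%
- DEFF 1.5: 11.0%
- DEFF 2.0: 16.6%
- DEFF 2.5: 21.5%
- DEFF 3.0: 25.8%

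So 7–22% corresponds to design effects of about 1.2 to 2.5. The formula is approximate: the simulated values at DEFF 2.5 were 18.3% and 23.6%.

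**The case against.** The best defence is that this is a condensed article that defers detail to a SAP. Cut-points, unit of analysis and handling of clustering are the kind of detail a SAP supplies. Severity is categorical, so worst grade per patient by arm is a legitimate Fisher table, and so is any rescue use. Number and degree by Poisson regression can be read as event rates by grade, with Fisher's test comparing the distribution of grades. Those would be two summaries and not a conflict.

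Much of this stands. For severity and rescue use, Fisher's test is not wrong in itself, and the two severity statements need clarifying rather than correcting. It does not stand for duration and interval. There the article names a test for outcomes that it defines on a different scale, and further detail on a mismatched method does not make it fit.

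A reader might go further and infer that Fisher's test, as planned, inflates type I error to 7–22% for all three outcomes. The documents do not support that. The article never says that events are pooled, gives no rate, dispersion or correlation from which to derive a figure, and with one value per patient there is no inflation. For a dichotomised time the harm is lost power.

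It is also true that duration and interval exist only in patients who had events after randomisation. That limits any per-event analysis. It is not a fault of Fisher's test, but it does bear on the choice of replacement.

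**Conclusion.** Wrong as written for duration and interval; unclear for severity. For the two times, a median split with Fisher's test would cost roughly 22 to 24 points of power against a rank test under the assumed sample sizes and shifts. For severity, inflation is conditional on pooling events. Over the assumed inputs it runs from none at zero correlation to above 30% at the extreme, with 7–22% as an illustration at design effects of about 1.2–2.5. The mismatch for duration and interval follows from the text alone; the sizes rest on assumptions that the documents neither give nor exclude.

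This should be fixed, but it does not threaten the main result. FEV1 and the number of exacerbations have separate methods, as does time to first exacerbation.

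**What to change.** Name one method per outcome in the SAP before database lock:

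- **Duration:** a method for time data that respects clustering by patient, either a rank test on one summary per patient or a patient-clustered model. Supplement it with total exacerbation days per patient-year in all randomised patients, zeros included, because per-event duration exists only in patients with an event. This adds to the listed outcome and does not replace it.
- **Interval:** a gap-time recurrent-event model with robust variance, which keeps the defined gap and handles the open last interval as censored.
- **Severity:** exposure-adjusted rates of moderate-or-severe events and of severe events, from the overdispersed count model already planned. State that this is what *degree* means.
- **Fisher's test:** keep it only for one-per-patient categories such as worst severity or any rescue use.

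The cost is revised method wording and a few extra model runs on event data already being collected. No change to the sample size or the visit schedule is needed.

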**Fig. 1 Fig1:**
[figure not shown]
Clinical trial design. COPD, chronic obstructive pulmonary disease; CAT, COPD assessment test; CCQ, COPD clinical questionnaire; mMRC, modified British Medical Research Council dyspnea scale

The primary endpoint includes the difference of FEV_1_ (including trough and peak) at 24 months from baseline and the number of acute exacerbations of COPD within 24 months between the two groups (mean values will be used in aggregation for the primary outcome data). Secondary endpoints include the following: trough and peak FEV_1_ at 12 months; the annual decline of FEV_1_, forced vital capacity (FVC), and FEV_1_/FVC (including trough and peak); duration, interval, and severity of COPD exacerbation; time to the first COPD exacerbation; quality of life (mMRC, CAT, and CCQ); medication administration and the use of rescue medications; and adverse events (Fig. 2).

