We aimed to assess the beneficial effects of long-term treatment with high-dose NAC in patients with early-stage COPD regarding exacerbation rates and pulmonary function. The primary outcome measurement is FEV1 and the rate of acute COPD exacerbation. Discontinuations will increase with increasing study duration in long-term trials, and the rates are usually higher in the placebo group. The placebo group discontinuation rates in the ISOLDE, EUROSCOP, and UPLIFT studies ranged from 30 to 53%. In line with the UPLIFT protocol, we have estimated that the discontinuation rate is 35% in our study [41]. To ensure that it will be adequately powered to enable evaluation of the primary outcome, each group needs at least 500 random patients. Considering the need for acute exacerbations and lung function, the total required sample size of the study was 1000 patients. The majority of participants enrolled have no or extremely minor symptoms, and the mere presence of respiratory symptoms or gradually reduced lung function is an insufficient reason for patients to seek medical help [41]. In addition to the planned drug delivery and follow-up, we will provide health education, including counseling them to quit smoking, informing them of the benefits of early treatment, and providing other health advice. We will establish a good relationship with the research subjects and conduct regular telephone follow-up or Internet supervision to reduce the withdrawal rate.

In summary, because a dose-effect association has been demonstrated for NAC, this NAC-COPD trial will provide an opportunity to explore the effect of twice-daily NAC in patients with early-stage COPD disease. We postulated that an increased dose of NAC might lead to improved outcomes.

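### The test named for rescue-drug use ignores follow-up time; if loss differs between arms the comparison tilts against the arm followed longer, by a modest amount at a plausible gap

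*Protocol article*

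**What the plan says.** The Study design section of the Protocol article lists "medication administration and the use of rescue medications" among the secondary endpoints. For the analysis, Sample size and statistical methods applies Fisher's exact test to the interval and duration of exacerbations, "severity, and the use of rescue drugs. The frequency of rescue drugs will be further described". No follow-up or exposure term is named for this endpoint.

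The same paragraph treats exacerbations differently. Counts are handled as follows: "The number and degree of acute exacerbation were compared by adjusted treatment exposure dose and over discrete Poisson regression". I read this as an overdispersed Poisson model adjusted for exposure. Time to first exacerbation gets a log-rank test.

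On loss, the sample size text applies one rate to both groups: "Assuming a 35% drop-off rate, each group needs to be randomized at least 489 patients". The Discussion remarks of long-term trials in general: "Discontinuations will increase with increasing study duration in long-term trials, and the rates are usually higher in the placebo group". It cites placebo-group discontinuation of 30 to 53% in three earlier trials and adopts 35% for this study.

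Under Measures, patients are asked about rescue drugs at each 3-monthly visit.

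**The concern.** Fisher's test needs categories, and the frequency of use is set apart for description. The tested variable is therefore most naturally whether a patient used a rescue drug at all. The chance of that grows with time observed. In such a table, a patient who leaves at month 5 and one observed for 24 months count equally.

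This does no harm to the level of the test if both arms are observed for the same time on average. If placebo patients leave more often, as the Discussion says is usual, NAC patients have more time in which a rescue drug can be recorded. NAC could then appear to raise rescue use when it has no effect, or a real reduction could be partly hidden. The article saw the need to account for time observed when it chose the exacerbation analyses, but names nothing comparable for rescue use.

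**Working it through.** **Inputs from the article.** 1000 patients allocated 1:1, so 500 per arm; 24 months of treatment; 35% loss; Fisher's test for rescue use; use asked about at each 3-monthly visit.

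**The plan's own figure.** With a difference of 100 ml, SD 450 ml, two-sided 5% and 80% power: n = 2 × (1.96 + 0.842)² × (450/100)² ≈ 318 per group, as stated. Dividing by 0.65 gives 489.2, against the stated 489. This confirms that the plan uses a single 35% in each group.

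**Assumptions, because the article gives no figures.** The rate of first rescue use h is constant at 0.15, 0.3 or 0.6 per year and the same in both arms. Dropout is uniform over the 24 months and unrelated to rescue use. Use after withdrawal is not recorded. All randomized patients are in the denominator. The split of loss is 30% on NAC and 40% on placebo, which keeps the average at 35%.

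**Formula.** With d the proportion lost:

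- completer: A = 1 − exp(−2h)
- leaver: B = 1 − (1 − exp(−2h))/(2h)
- recorded as a user: P = (1 − d)A + dB

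With no drug effect the arms differ by (d_placebo − d_NAC)(A − B).

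**Size of the bias, 30% v 40% loss, no drug effect.**

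| h per year | A | B | NAC | Placebo | Difference |
|---|---|---|---|---|---|
| 0.15 | 0.259 | 0.136 | 0.222 | 0.210 | 1.2 points |
| 0.3 | 0.451 | 0.248 | 0.390 | 0.370 | 2.0 points |
| 0.6 | 0.699 | 0.418 | 0.614 | 0.586 | 2.8 points |

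With equal loss the difference is zero at every h.

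**False rejection at nominal 5%, simulated, 500 per arm.**

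- Equal loss of 35%: about 4 to 5%. The test keeps its level.
- 30% v 40%: 7.2%, 9.1% and 13.1% for the three rates, nearly all showing NAC as worse.
- A log-rank test of time to first use on the same kind of data: about 4 to 7% over two sets of runs.

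**Power.**

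- True hazard ratio 0.75 and 30% v 40% loss: Fisher's test has 44% and 56% power at h = 0.3 and 0.6; log-rank has 74% and 92%.
- Not all of that gap is bias. At h = 0.6 with equal loss, Fisher's test has 84% against 92% for log-rank. Unequal loss accounts for the fall from 84% to 56%.

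**Different dropout shape.** With exponential dropout, mean follow-up is 1.68 years on NAC (30% loss) and 1.57 on placebo (40%). If 24-month use under full follow-up is 20, 40, 60 or 80%, false rejection is 6, 10, 15 and 22%. At 40% use, recorded users are 34.2% on NAC and 32.0% on placebo. With a true 20% lower rate on NAC, Fisher's power falls from 47% under equal loss to 19%.

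**The case against.** The strongest objection is that the plan does not assume unequal loss. It applies one 35% to both groups, and under that assumption Fisher's test is valid. The sentence saying that "the rates are usually higher in the placebo group" is a general remark, and the 30 to 53% range covers placebo groups only, so it yields no gap between arms. The Discussion also describes efforts to reduce withdrawal. All of this stands, and it makes the point conditional.

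A reader might infer that the plan forecasts heavier loss on placebo in this trial, so that the test will reject too often against NAC. The documents do not support that. A reader might also reach for a wider gap: with 25% v 45% loss, false rejection would be 15 to 42%. No part of the article gives such a split.

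Second, users versus non-users over 24 months is an inference. A visit-by-visit table among attenders would also be a Fisher table and would largely avoid the problem. Yet the article describes no such analysis, and ever-use is the plainer reading. Telephone follow-up is mentioned as a way to limit withdrawal; whether it would capture rescue use after withdrawal is not said.

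Third, a separate statistical analysis plan is announced and could add the adjustment. True, but this is not a detail merely left open: the article names a test that has no place for follow-up time.

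Fourth, log-rank and rate models are themselves biased if patients leave because they are getting worse. That stands as a limit on the remedy.

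Last, the consequence is small. Rescue use does not appear among the key secondary outcomes in Table 1, and no sample size or decision rule rests on it.

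**Conclusion.** The point holds in a conditional form, as a cheap improvement. Fisher's test of rescue-drug users takes no account of time observed. With equal loss it keeps its level. If NAC patients are followed longer and use after withdrawal is not recorded, it is biased against NAC. At an assumed 30% v 40% loss and first-use rates of 0.15 to 0.6 per year, the bias is about 1 to 3 percentage points and false rejection about 7 to 13% instead of 5%, with reduced power for a true benefit. A wider gap, which the documents do not state, would make this worse. The use rates, the split of loss and the dropout shape are all assumptions. The primary conclusions are unaffected.

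**What to change.** In the statistical analysis plan, make the main test of rescue use one that accounts for follow-up, as the article already does for exacerbations. Two options would serve:

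- time to first rescue use, by log-rank test, or by a discrete-time model on the 3-monthly intervals if exact dates are not recorded;
- rescue courses or days per patient-year, in a count model with log follow-up time as offset.

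State how use is defined and whether it is recorded after withdrawal. Keep the percentage of users in each arm as description, beside the person-time observed.

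The cost is a sentence or two, since medication use is already collected at every visit. There are two downsides: timing may be known only to the nearest 3 months, and either method removes the bias only if dropout is non-informative.

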### Ethics and dissemination

This study was approved by the Ethics Committee of The First Affiliated Hospital of Guangzhou Medical University. Recruitment into this clinical trial started in September 2017 with a targeted completion date of August 2019. The follow-up of NAC treatment is currently ongoing, and the last trial visit of the last participants is scheduled to occur in September 2021 (Table 1). The study findings will be presented at conferences and reported in peer-reviewed journals.

**Table 1 Tab1:** Trial registration data

Data category	Information
Primary registry and trial identifying number	Chinese Clinical Trial Registry: ChiCTR-IIR-17012604
Date of registration in primary registry	07 September 2017
Secondary identifying numbers	NA
Source(s) of monetary or material support	Ministry of Science and Technology, China
Primary sponsor	The First Affiliated Hospital of Guangzhou Medical University
Secondary sponsor(s)	The First Affiliated Hospital of Guangzhou Medical University
Contact for public queries	[name], [contact]
Contact for scientific queries	[name], [contact]
Public title	Long-term regular treatment of early COPD with Acetylcysteine effervescent tablets: a randomized, double-blind, placebo-controlled multicenter clinical study
Scientific title	Long-term regular treatment of early COPD with Acetylcysteine effervescent tablets: a randomized, double-blind, placebo-controlled multicenter clinical study
Countries of recruitment	China
Health condition(s) or problem(s) studied	Chronic obstructive pulmonary disease
Intervention(s)	Active comparator: *N*-acetylcysteine effervescent tablets (1200 mg per day)
	Placebo comparator: microcristallin cellulose (matching tablets containing no active ingredients)
Key inclusion and exclusion criteria	Aged 40–80 years old, male or female, community or outpatient
	Has respiratory symptoms (chronic cough, sputum, shortness of breath) and/or chronic obstructive pulmonary exposure risk factors (smoking, occupational exposure, indoor and outdoor air pollution, family history of chronic obstructive pulmonary disease, recurrent respiratory tract infection, low birth weight, and genetic factors, etc.)
	GOLD stages I–II, COPD: FEV_1_/FVC < 70% and FEV_1_ ≥ 50% predicted after 20 min with 400 μg of salbutamol inhalation
Study type	Interventional
	Allocation: randomized; intervention model: parallel assignment; masking: double blind
	Primary purpose: prevention
	Phase IV
Date of first enrolment	September 2017
Target sample size	1000
Recruitment status	Recruiting
Primary outcome(s)	The difference of FEV_1_ (including trough and peak) at 24 months from baseline and the number of acute exacerbations COPD within 24 months between two groups
Key secondary outcomes	Annual decline of FEV_1_, forced vital capacity (FVC) and FEV_1_/FVC (including trough and peak); duration, interval, and severity of COPD exacerbations

